## Abstract

**Background:**

Dementia is an incurable disease with devastating consequences for both patients and their relatives. The objective of this study is to describe the study protocol of a randomized controlled trial with assignment to either usual care or case-management by district nurses, among informal caregivers of older adults with dementia symptoms who live at home and the older adults who receive informal care.

**Methods/design:**

In this randomized controlled trial, effectiveness as well as cost-effectiveness of case-management is evaluated. It concerns case-management in early-detected patients with dementia symptoms and their primary informal caregivers. Participants are followed up to twelve months after baseline assessment. The main outcome measure of the effect evaluation is the caregiver's sense of competence to care for the older person with dementia symptoms. The economic evaluation is performed from a societal perspective.

**Discussion:**

This is one of the first trials on case-management that includes an economic evaluation. In addition, it concerns a tailor-made intervention in early-detected patients with dementia symptoms and their caregivers. The results of this randomized controlled trial will provide valuable information for health professionals and policy makers on effectiveness and cost-effectiveness of early tailor-made case-management for patients and their informal caregivers. Moreover, positive effects will challenge current health care systems to move to more pro-active approaches for this group.

## Background

Dementia is a major public health problem with enormous costs to society [1]. It is an incurable progressive disease with devastating consequences for both patients and their relatives. The estimated prevalence rate of dementia among older adults aged 65 to 95 is 6.6% [2]. Over the next years the number of demented older persons will increase substantially as a result of aging populations [3].

Initially, informal caregivers, such as relatives, neighbors and friends, care for most patients with dementia. Caregiving is generally unplanned and most informal caregivers gradually adopt their role because of the insidious nature of dementia [4]. However, informal caregivers often experience adverse psychological, physical, social, and financial consequences [5]. Compared with non-caregivers, they live shorter and report more depressive symptoms [6,7]. Besides, caring for a demented person is marked by losses of previous roles in a relationship. Moreover, many caregivers reduce or give-up the time spent on paid jobs and social activities [4].

Timely detection of dementia is important for both patients and their caregivers as it enables care support and prepares future care [8]. However, there is evidence of underdetection [9,10] and diagnostic delay [11]. An important patient related barrier to timely recognition is the absence of a request for help. This absence can be attributed to denial, labeling cognitive impairment as an accepted aspect of normal ageing, lack of awareness of the disease process, or the idea that nothing can be done [12,13]. In contrast to conventional care, pro-active care with timely detection followed by structured care focusing on both demented patients and informal caregivers, may be more suitable for this vulnerable group. So far, randomized controlled trials of such pro-active disease management systems have not been reported. Yet, up till now, to assist informal caregivers of demented older adults, several psychosocial support programs have been developed, such as support groups, respite care, stress-management, social skills training, psycho-educational groups, and case-management. On the whole, multicomponent interventions that provide caregivers with diverse services and supports, and individually tailored interventions showed larger effects on caregivers' well-being than other, narrowly focused interventions [14-18]. We use the concept 'sense of competence' to denote the caregiver's feeling of being capable to care for the demented person.

Interventions showed increased caregivers' sense of competence [19,20], stabilized caregivers' well-being [21,22] to sustained benefit in reducing depressive symptoms [23], changed caregiver's appraisals of patient behavioral problems [24], and, lastly, postponement of patients' institutionalization [19,20,25-28], although there is lack of strong findings in general [18,29,30]. Trials on case-management, showed a deferral or no reduction in patients' institutionalization rate [27,31], and on the whole did not impact caregivers' levels of depression and burden, in spite of small reductions at some sites [21]. Few studies have performed economic evaluations of interventions for community-dwelling dementia patients [32-34]. Cost-effectiveness analyses and cost-utility analyses are even rare [35].

An innovative initiative to support dementia patients and their caregivers was set up by the Department of General Practice of the VU University medical center, GPs and district nurses in West-Friesland, the Netherlands. We developed a pro-active program, in which the key elements consist of timely detection of dementia symptoms followed by case-management by district nurses among detected patients and their primary informal caregivers. A randomized controlled trial (RCT) is performed to observe effectiveness and cost-effectiveness of case-management.

The objective of this paper was to describe the study protocol of this RCT among informal caregivers of men and women aged 65 years or over with dementia symptoms who live at home, and the men and women they take care of. The main research questions of this RCT concern whether case-management is more effective than usual care in improving caregiver's sense of competence, and whether case-management is cost-effective compared to usual care when assessed from a societal perspective. A secondary research question is whether case-management is more effective than usual care in improving caregiver's quality of life, caregiver's psychological well-being, caregiver's burden, patient's quality of life, and in decreasing hospital days, days until institutionalization and death of the patients.

## Methods/design

### Design

The design is a RCT with assignment to either usual care or case-management by district nurses among patients with dementia symptoms and their primary informal caregivers. Figure 1 shows the design of the study. Participants are only allowed to enter the study after signed informed consent. Representatives give informed consent of incompetent patients. The Medical Ethics Committee of the VU University medical center in Amsterdam approved the study.

**Figure 1 F1:**
[figure not shown]
Design

### Participants

Detection of patients and subsequent recruitment of their informal caregivers takes place among GP patients in West-Friesland, the Netherlands. Patients are potentially eligible for trial entry ifthey are 65 years or over, live outside of institutional settings, and suffer from dementia symptoms. Patients with dementia symptoms have multiple cognitive impairments (i.e. memory impairments, aphasia, apraxia, agnosia, and impairment in executive functioning). These symptoms lead to significant limitations in social functioning and progressive decline in general functioning. Two sources are used to detect patients; 1) Caseload of co-operating GPs. 2) The primary care Diabetic Research Center in which all GPs of West-Friesland participate. Detection of patients takes place in four ways, as shown in Figure 2. 1) GPs who are willing to co-operate, provide a list of addresses of all their patients, aged 75 or over and living at home. All patients receive a postal health questionnaire in order to identify older adults with cognitive decline, as assessed with a self-report version of the short Informant Questionnaire on Cognitive Decline (IQCODE) [36]. 2) Co-operating GPs mark patients who they suspect of dementia on the list of addresses they provide. 3) All GPs in West-Friesland invite patients suspected of dementia after consultation, for a cognitive assessment. 4) The primary care Diabetic Research Center provides addresses of their community-dwelling diabetic patients aged 65 or over and not approached formerly. Older patients with diabetes mellitus are more at risk of dementia and cognitive decline than those with normal glucose tolerance [37]. Diabetic patients also receive an IQCODE.

**Figure 2 F2:**
[figure not shown]
Recruitment of the Study Population

Patients with an IQCODE score of 3.6 or over (strongly suggesting cognitive decline), and patients suspected of dementia by their GP, are assessed at home with the 7 minute screen (7MS) [38] and the Mini Mental State Examination (MMSE) [39]. Patients who score less than 24 on the MMSE or who have a probability of having dementia of 50% or more according to the 7MS, are considered eligible for trial entry. If an eligible patient has more than one informal caregiver, the primary caregiver is the one who spends most hours on caregiver tasks and who coordinates the caring process. Exclusion criteria for patients applied at baseline are: assistance by an outpatient geriatric team for cognitive problems, terminal illness, insufficient command of the Dutch language, participation in other research projects, and institutionalization. Exclusion criteria for caregivers are: terminal illness and insufficient command of the Dutch language. Recruitment commenced in spring 2003 and ended in summer 2005.

### Randomization

Randomization takes place after baseline measurement. An external independent person establishes the random order using random number tables. Blocking by practice (blocks of four) is used to ensure that comparison groups are of approximately the same size per practice.

### Intervention

During one year, three district nurses who are specialized in geriatric care, act as case-manager of both patient and informal caregiver. Case-management entails assessment, planning, coordination, collaboration, and monitoring of care. Nurses provide practical, informational and socio-emotional support. Multiple support strategies (e.g. support groups, respite care) are offered to informal caregivers and patients. The nurses start the intervention with a home-visit in which they administer a patient assessment; the Resident Assessment Instrument Home Care (RAI-HC). The RAI-HC is a computerized multidimensional instrument that consists of a Minimum Data Set (MDS) that assesses general functioning of the patient, and Client Assessment Protocols (CAPS), providing protocols for the management of 30 potential and actual problem areas [40]. Together with the participants, the nurses order the identified problems of the RAI into a hierarchy, and formulate a care-plan for these problems. Subsequently, they leave behind a form to register care received and appointments with health professionals. In the second home-visit, nurses explore the caregiver's situation with a capacity and burden questionnaire [41] and hand a guide to caregivers holding available social services and welfare professionals. The nurses formulate a care plan for the informal caregiver based on the capacity and burden questionnaire. After these two visits, the nurses and participants decide how they want to proceed with the intervention. When more visits are not necessary, the nurses contact the participants at least every 3 months to monitor their situation. The nurses leave a dossier at the patient's house. This dossier contains the care plan, identified problems by RAI assessment and notes of planned and undertaken activities. Other visiting health professionals may take notice of the dossier and add their own notes. The nurses contact the GPs to inform them about the situation. Apart from these compulsory activities, the intervention holds some tailor-made activities. When necessary, nurses refer to other health professionals, including diagnostic services and monitor the anticipated effect. In addition, the nurses may organize family-meetings to educate relatives, improve social support and relieve the caregiver [4]. Nurses were trained in working with the computerized RAI-HC, and in organizing family-meetings. They also received seminars on how to deal with dementia patients and their patients. They meet monthly to discuss innovations and geriatric cases while supervised by a staff member. Nurses provide care according to a National Guideline on dementia for district nurses [42].

### Usual care

Patients and informal caregivers in the control group receive usual care. In the Netherlands, all people are registered in a primary care practice. General practitioners, as well as a regional indication institution act as gatekeepers of the Dutch health care system. GPs provide cure according to the Guideline on dementia of the Dutch College of General Practitioners. They aim to diagnose and inform dementia patients and their relatives preferably at an early stage [43]. However, guideline recommendations in general, are followed in on average 67% of the decisions [44]. Co-operating GPs are unaware of patients allocated to usual care, unless participants reveal their allocation. Participants of the usual care group have no access to most of the structured and tailor-made activities of the intervention (e.g. family meetings, RAI-HC assessment, guide for informal caregivers). In the region of research, suspected patients are referred to mental health professionals, never to district nurses. All participants of the usual care group are offered the intervention after the one-year follow-up.

### Measurements

Table 1 provides an overview of all effect and economic measurements. At baseline (T0), and after 6 (T1) and 12 months (T2) trained interviewers visit participants. At baseline and after 6 months, they leave cost diaries for patients and caregivers to register medical consumption during the successive 6 months. These cost diaries also provide the possibility to visualize delivery of the intervention and usual care. When patients are unable to fill out a questionnaire, their informal caregiver is allowed to fill it out or to provide assistance.

**Table 1 T1:** Measurement Scheme

**variable**	**Instrument**	**T0**	**T1**	**T2**

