### Blinding

Interviewers are kept blind from the randomization status of participants. GPs can be unaware of patients allocated to the usual care group, but they will be aware of patients in the intervention group as nurses contact the GP about these patients. Participants are not blinded.

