### Analysis

#### Effect evaluation

Data are primary analyzed according to the intention-to-treat principle. Additionally, data are analyzed according to the on-treatment (i.e. per protocol) principle in order to examine whether protocol deviations have caused bias. General Linear Models are used to analyze differences between the intervention and usual care group on caregiver's sense of competence, caregiver's quality of life and caregiver's psychological well-being. Potential baseline differences are accounted for by covariates. Differences in days until institutionalization and death between patients of the two groups are tested with survival analyses (Cox-proportional hazard modeling). Differences on patient's hospitalization days and patient's quality of life are tested by a chi-square test and student t-test, respectively. Potential confounding is checked, including the effect of different interviewers and nurses.

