Secondly, two situations may cause information bias. Firstly, bias may occur as cognitively impaired subjects without insight may fill out questionnaires. However, as we assume that detected patients suffer mainly from mild or moderate dementia symptoms, and insight is mainly preserved in these subjects, this bias probably will be limited. Secondly, in the economic evaluation, caregivers are allowed to provide assistance or to fill out the EQ-5D when patients are unable to fill out this questionnaire. This may lead to information bias, as it is known that agreement on the EQ-5D between patients and caregivers is poor [64]. However, this bias probably will be limited as well, as we assume that detected patients suffer mainly from mild or moderate dementia symptoms, and most patients will fill out the questionnaire themselves.

Thirdly, contamination could bias results of this study as we choose to perform randomization on patient level. However, influence of contamination on results is unlikely as participants of the usual care group have no access to particular activities of the intervention (e.g. family meetings, RAI-HC assessment, guide for informal caregivers). Nevertheless, it is possible that participating GPs are encouraged by the project to give more attention to patients with dementia symptoms and their informal caregivers participating in the usual care group.

Lastly, we expect heterogeneity in study subjects because response to interventions may be different depending on caregiver circumstances. In combination with the relatively small sample size of approximately 100 participants, this heterogeneity may make it hard to interpret the outcomes. However, increasing the sample size is not feasible. Therefore, we will visualize distribution of characterizes over comparison groups to estimate the influence of this heterogeneity on outcome measures. Moreover, cost diaries will detect heterogeneity in received care within the usual care group as well as in the case-management group.

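### Patient quality-of-life and utility scores may come from an unblinded caregiver who is also treated, and the stated t-test uses neither the baseline score nor the respondent

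*Protocol article*

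**What the plan says.** The Measurements section sets the rule for patient questionnaires: "When patients are unable to fill out a questionnaire, their informal caregiver is allowed to fill it out or to provide assistance". No instrument is exempted. Table 1 lists the DQOL and the EQ-5D for the patient at T0, T1 and T2.

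On the proxy's position, the Blinding section says "Participants are not blinded". The Intervention section makes the nurses case-managers of the caregiver as well as the patient.

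On analysis, the Effect evaluation text under Analysis says: "Differences on patient's hospitalization days and patient's quality of life are tested by a chi-square test and student t-test, respectively". General Linear Models, with covariates for baseline differences, are named for caregiver outcomes only. The Economic evaluation section derives utilities from the EQ-5D for a separate patient cost-utility analysis.

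The Discussion takes up the issue for one instrument, noting that "caregivers are allowed to provide assistance or to fill out the EQ-5D when patients are unable to fill out this questionnaire". It adds: "This may lead to information bias, as it is known that agreement on the EQ-5D between patients and caregivers is poor". It then judges the bias to be small "as we assume that detected patients suffer mainly from mild or moderate dementia symptoms", and because "most patients will fill out the questionnaire themselves".

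**The concern.** A patient score can be the patient's own answer, an assisted answer or the caregiver's answer, and the mix can change between visits in a progressive condition. Blinded interviewers do not protect a score whose rater knows the allocation. In the case-management arm that rater is also the person whose own sense of competence the intervention aims to improve. A better-supported caregiver might rate the same patient more favourably.

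The Discussion's reassurance leaves three gaps. It does not discuss proxy completion of the DQOL. It does not mention that the proxy is unblinded and treated. Its severity assumption is not secured by the entry rules: the Participants section gives no lower MMSE limit, and the Design section admits incompetent patients through representatives.

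At stake are the patient quality-of-life result, which is secondary, and the patient cost-utility analysis. The latter belongs to the cost-effectiveness question, which the Background names among the main research questions.

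**Working it through.** **Plan's own figure.** The article gives no proxy share and no SD for the DQOL or EQ-5D, so there is no figure to reproduce on this point. The only available group size is the 37 per group planned for the SCQ. That figure reproduces: 15% of the scale range is 0.15 × (27 − 4) = 3.45. With SD 5.2, two-sided 0.05 and power 0.80, this gives 36 per group by the normal approximation and 37 by the t-test. I use 37 below only to show scale.

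**When mixing respondents becomes bias.** Let p1 and p0 be the proxy shares under case-management and usual care. Let o be the proxy-minus-self offset common to both arms, and g any extra shift in ratings by case-management proxies, both in SD units. With no true effect:

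bias = p1 × (o + g) − p0 × o = (p1 − p0) × o + p1 × g

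If p1 = p0 and g = 0, the bias is zero. Mixed respondents then add noise only.

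**Effect on a two-sided 5% t-test.** With 37 per arm, the noncentrality is bias / √(2/37) = bias / 0.2325, on 72 degrees of freedom. The shares and shifts are assumptions.

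| Assumed situation | Bias (SD) | Rejection with no true effect |
|---|---|---|
| Equal shares, no rating shift | 0 | 5.0% |
| Share 10% in both arms, g = 0.5 | 0.10 × 0.5 = 0.05 | 5.5% |
| Share 20% in both arms, g = 0.5 | 0.20 × 0.5 = 0.10 | 7.1% |
| Share 30% in both arms, g = 0.5 | 0.30 × 0.5 = 0.15 | 9.8% |
| Share 50% in both arms, g = 0.5 | 0.50 × 0.5 = 0.25 | 18.6% |
| Shares differ by 20 points, o = 0.5, g = 0 | 0.20 × 0.5 = 0.10 | 7.1% |
| Share 50% in both arms, g = 1 (extreme) | 0.50 × 1 = 0.50 | 56.4% |

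**From utility to QALY.** A utility difference at T2 is not a QALY difference. With visits at 0, 6 and 12 months, linear interpolation (an assumption) and no difference at T0, a T2 difference d gives:
- 0.25d if it appears only at T2;
- 0.5d if it grows linearly;
- 0.75d if it is fully present from T1.

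With an assumed EQ-5D SD of 0.2, a bias of 0.10 SD is 0.10 × 0.2 = 0.02 utility, or 0.005 to 0.015 QALY.

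**The case against.** The strongest reply is that the article already discloses the risk for the EQ-5D and gives a reason to expect it to be small, and that respondent coding and sensitivity analyses are commonly left to a fuller document. The second part stands: the absence of such detail is not the point here. The point is what the article fixes, namely the mixed-respondent rule, an unadjusted t-test, and reliance on an assumption about severity.

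Other parts also stand:
- DQOL proxy completion is inferred from the general wording of the rule. The Discussion names only the EQ-5D.
- The t-test most clearly covers the DQOL. The EQ-5D enters the economic evaluation through bootstrapped ratios, so the two instruments reach bias by different routes.
- The analysis section promises a check of potential confounding. It names interviewers and nurses but not respondent, and a t-test cannot carry the adjustment.
- Several entry features favour milder cases: patients live outside institutions, those assisted by an outpatient geriatric team for cognitive problems are excluded, and patients with an MMSE of 24 or more can enter through the 7MS. They make the severity assumption reasonable without guaranteeing it.

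A reader might infer that the bias is differential because the proxy knows the allocation. The documents do not support that. Lack of blinding makes differential rating possible; it does not show that it happens. Patients are unblinded too, so self-report shares that weakness. A reader might also infer that moving from self-report to proxy during follow-up biases the comparison in itself. It does so only if the share or rating differs by arm, and the article gives no figures on either.

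**Conclusion.** The point holds as a conditional weakness. The article lets an unblinded caregiver, who is treated in one arm, supply or help with patient scores, and it names a test for patient quality of life that ignores baseline and respondent. If proxy share or proxy rating differs by arm, the patient quality-of-life and utility comparisons can be biased, in either direction.

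The size cannot be derived from the documents. Under the assumptions shown, the distortion is slight at a 10% proxy share and becomes material only with a large share or a large rating shift. The primary SCQ analysis is the caregiver's own report and is not touched. This is worth correcting because the remedy is cheap, not because the trial's main conclusion is in danger.

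**What to change.** 1. Record at T0, T1 and T2 whether each patient questionnaire was self-completed, assisted or proxy-completed.
2. Replace the t-test for patient quality of life with a linear model containing arm, T0 score and T0 respondent mode, and adjust the patient utility comparison the same way. Randomization follows the baseline measurement, so neither covariate can be affected by allocation.
3. Keep all respondents in the main analysis. Setting lost self-reports to missing would create outcome-related missingness in a small trial.
4. Add a sensitivity analysis on self-reported values, labelled as conditioning on a post-randomisation variable.
5. In place of the assumption that the bias is small, commit to reporting the respondent mix by arm and visit.

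The model does not remove differential rating by unblinded proxies or switching after T0. Items 4 and 5 let a reader judge how much room there is for either.

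The cost is one tick-box per questionnaire and a few extra model runs; T0 scores are already collected. The article reports that recruitment has ended, so if the T0 forms did not capture mode, it would have to be reconstructed from interview records or coded as unknown.
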